This will involve collection of routine program monitoring data on utilization of family planning, postpartum/postnatal and HIV services. Forms will be used to extract client register data on a monthly basis for further analysis. Analysis of routine program data will contribute to answering the following questions: 1) what is the change in client profile pre- and post-integration (for instance, in terms of age, and sex)?, 2) does the rate of new clients accessing the services increase post-integration?, and 3) what are the changes in range of service uptake and client-profile pre- and post-integration across a range of SRH/HIV services.

c) Costing of service delivery across the different models

In each of the study facilities, the costs of delivering integrated SRH-HIV services will be measured both at baseline and endline, and the potential for efficiency gains will be assessed. Where feasible these cost data will be combined with an effectiveness analysis (with client and population level data) to estimate the cost-effectiveness of integrated services.

A periodic activity review (PAR) tool will be used to provide a mapping of how resources are combined to produce integrated HIV and SRH services in each study facility at baseline. The tool will include questions on facility characteristics, staffing types and levels, scope and number of services offered, clinical practice, descriptions of client flow, and overall description of how integration of services works from the provider’s perspective. Building on the PAR, the unit cost study will estimate the quantity and value of resources that are used to implement activities at facility level. Costing tools will be developed from the first round of data from the PAR, but will generally be based on UNAIDS costing guidelines: *The Costing Guidelines for HIV Prevention Strategies*[33].

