A standard ingredients approach will be used. Bottom up methods will be used to estimate the direct costs of each service, and these will be combined with top-down method for the costs of overhead resources. In hospital settings, a step-down approach will be used for costs estimated through the top-down approach. The findings will be used to explore whether there are economies of scope and scale associated with the provision of an integrated package of SRH services, and to explore the relative efficiency of different models of provision. The cost data will be used to conduct an econometric analysis to estimate the impact of different cost drivers, including the extent of integration. This is the first time an economic study of this type will be used to evaluate integrated services [34].

d) Cohort study of clients

After the completion of the post-intervention HFA, two samples of clients accessing PNC and FP services (from intervention and comparison facilities) will be recruited and followed over a two-year period, interviewed up to 4 times. Various indicators will be monitored in these populations, including: condom and contraceptive use, fertility intentions, use of PNC and FP services, HIV status, unintended pregnancy, and SRH behaviors. To be eligible for inclusion in the FP-HIV study, the women will be aged 15 years and over, be revisit FP clients, be living in the catchment area of the health facility, and willing to give their informed consent to be interviewed. For the PNC-HIV model, the women will be aged 15 years and over, be clients attending a postnatal check for themselves and/or their infant (0–10 weeks), be living in the catchment area of the health facility, and willing to give their informed consent to be interviewed.

Cohort recruitment: Table 2 summarises the sample sizes that will be sought for the cohort studies. The minimum sample size will be based on 80% power to detect an increase in reported condom use (the key indicator/outcome that required the largest sample) from 5% to 10% in Kenya, with estimates of treatment effect derived from other studies in Kenya [18,20]; and from 13% to 20% in Swaziland, based on estimates from the 2006–2007 Swaziland Demographic and Health Survey (SDHS) [26]. The other outcome to be measured from these data is unintended pregnancies; since this required a smaller sample size it is covered within the condom use sample.

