To evaluate exposure to integrated services, an ‘index of integration’ will be developed. A generalized latent variable will be modeled using data from the client flow analysis and costing tools and validated by testing it against expert opinion (both researchers and service practitioners), to give each clinic a ranking score for its level of integration at various points in the study cycle. The index will be used to: a) assess changes in the extent of integration within each facility over time (whether originally allocated as intervention or not); b) control for baseline differences in integration when comparing outcomes in intervention and comparison facilities; and c) measure changes in the extent of integration over time and apply as a time-varying exposure in the dose–response analysis described above.

Qualitative data will be captured in digitally recorded files, transcribed and translated (where needed), before being exported into QSR Nvivo 8 software for management and analysis. A thematic framework will be used in qualitative analysis, allowing a fusion of both a deductive approach, with themes pre-identified from the study objectives, and an inductive approach, with themes emerging from the data incorporated into ongoing analyses.

The economics findings will be used to explore whether there are economies of scope and scale associated with the provision of an integrated package of SRH-HIV services, and to explore the relative efficiency of different models of provision. Cost data will be captured in specially designed Excel spreadsheets. These will then be entered into a STATA dataset. The impact of integration on efficiency will be assessed using a combination of parametric and non-parametric methods. Descriptive cost and resource use analysis, uni-variate analysis and Data Envelopment Analysis (DEA) will be used to identify those clinics that are more or less efficient; changes in unit costs, resource use, resource sharing and efficiency between baseline and endline; and to explore possible explanations for efficiency changes. Intervention and comparison sites will be compared, but also within these different sites with one another.

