In addition, a multi-level multivariable logistic regression analysis will be used to explore any association between unit costs, the intervention and integration. This will first explore the relationship between patient level characteristics and costs (derived from a combination of cohort data with cost data) and then, taking this into account, between facility level characteristics and costs. The integration index will be included as a facility level characteristic. Data from the cohort study will provide client level characteristics and service use. This will be combined with the unit cost data to estimate client level (health service) costs. Data from the periodic activity review data and health facility assessments will be used to define facility characteristics.

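### The integration index may share data with the unit costs it is meant to explain, and it is described as a ranking although it has to measure change over time

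*Protocol article*

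**What the plan says.** In the section Data management and analysis, the protocol article introduces an index of integration as its measure of exposure to integrated services. On inputs: "A generalized latent variable will be modeled using data from the client flow analysis and costing tools". On output, the aim is "to give each clinic a ranking score for its level of integration at various points in the study cycle". The section then lists three uses:

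- to "assess changes in the extent of integration within each facility over time", in every clinic whatever its original allocation;
- to adjust for baseline differences between intervention and comparison facilities;
- to "measure changes in the extent of integration over time and apply as a time-varying exposure" in the cohort dose-response analysis.

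A fourth use comes at the end of the same section, in a regression meant to "explore any association between unit costs, the intervention and integration". There the article says: "The integration index will be included as a facility level characteristic". The costing subsection (Description of methods and data collection, item c) gives integration the same role, since its econometric analysis is to "estimate the impact of different cost drivers, including the extent of integration".

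That subsection also describes the costing tools. They are developed from a periodic activity review covering, among other things, staffing, the services on offer and how clients move through the clinic. The unit-cost study that follows records how much of each resource is used and what it is worth. The article does not say which costing-tool items go into the index.

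**The concern.** There are two separate problems.

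**Shared inputs in the cost model.** A unit cost is the value of resources used divided by the number of services or clients. If an index item is also part of that numerator or denominator, the index and the unit cost are correlated by construction, even where integration has no effect on cost. Staffing is an example: it can indicate capacity to integrate, and it is also a resource that unit costs value. The sign of the induced association depends on the item, so it could look like an efficiency gain or an efficiency loss. Objective 3 depends on this analysis.

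**A rank as a measure of change.** A rank places a clinic relative to the others in the same round. It cannot show all clinics integrating together, and it drops for a stable clinic that others overtake. The article expects such shared movement. Under Approach and conceptual framework it describes policy on integration as still developing, some clinics as already partly integrated, and comparison sites as open to contamination. Dose-response is one of the five strands of evidence listed there for plausibility, and one of the two survival approaches for the cohort.

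**Working it through.** The plan states no figure on this point, so there is nothing to reproduce. The checks below are illustrations under stated assumptions.

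**1. Shared inputs**

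Inputs from the article: 12 facilities per Kenya model, hence 24 in Kenya, and 8 in Swaziland (Table 2 and the provider-interview subsection), 32 in all. A footnote to Table 2 adds 2 facilities to the Swaziland figure later; this is not used here.

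Assumptions: true integration T and unit cost C are independent standard normal variables, so any association found is false.

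- Client-flow score: F = 0.8T + 0.6e, with e standard normal.
- Costing item: K = ρC + √(1−ρ²)(0.8T + 0.6e′), with e′ standard normal, so K has correlation ρ with unit cost.
- Index: (1−w)F + wK, where w is the weight on the costing item.

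The induced correlation between index and cost is

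r = wρ / √[(1−w)² + w² + 2w(1−w)·0.64·√(1−ρ²)].

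For w = 0.25 and ρ = 0.3: 0.075 / √0.854 = 0.08. For w = 0.5 and ρ = 0.6: 0.30 / √0.756 = 0.345.

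The rate at which a two-sided 5% Pearson test rejects, over 4,000 simulated runs per cell, was:

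| w | ρ | 12 facilities | 24 facilities | 32 facilities |
|---|---|---|---|---|
| 0.25 | 0.3 | 0.052 | 0.069 | 0.074 |
| 0.25 | 0.6 | 0.077 | 0.125 | 0.146 |
| 0.5 | 0.3 | 0.080 | 0.125 | 0.155 |
| 0.5 | 0.6 | 0.202 | 0.388 | 0.501 |

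With w = 0 or ρ = 0 the rate stayed between 0.043 and 0.056. The simulation error at 5% is √(0.05 × 0.95 / 4000) = 0.0034, so 0.052 cannot be told apart from no problem. The error grows with the number of facilities, because a fixed false correlation is detected more easily. The planned analysis is a multi-level regression; a facility-level correlation is a simplification of it.

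**2. Ranks**

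Ranks 1 to n always sum to n(n+1)/2:

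- 12 clinics: 12 × 13 / 2 = 78, mean 6.5.
- 8 clinics: 8 × 9 / 2 = 36, mean 4.5.
- 10 clinics, if the 2 added Swaziland facilities are ranked as well: 10 × 11 / 2 = 55, mean 5.5.

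The sum is the same in every round, so the mean change in rank is exactly 0.

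A second simulation used 12 clinics (6 + 6), latent scores with SD 1 and no measurement error, over 4,000 runs:

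| True change, intervention / comparison (SD) | Mean rank change, intervention / comparison |
|---|---|
| +1 / +1 | 0 / 0 |
| +1 / 0 | +1.56 / −1.56 |
| +1.5 / +0.5 | +1.58 / −1.58 |

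The last two rows are nearly the same on ranks. Comparison clinics that were stable, and comparison clinics that improved by half an SD, both appear to lose about 1.6 places.

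**The case against.** The strongest reply is that the wording leaves room for a sound method, and that a condensed article need not list index items. Several parts of it stand.

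- **A reader might infer that the index is circular for cost.** The article does not establish this. The periodic activity review behind the costing tools holds many items that are structural, not monetary, and these can be reasonable indicators of integration. The table above runs from negligible to serious on assumed values of w and ρ alone.
- **A reader might infer that the exposure is wrongly scaled.** A latent variable model normally gives a continuous score, and the ranking may only mean that clinics are ordered by it. Nothing says that scores will be replaced by integers in each round.
- **A reader might infer that cohort dose-response results are invalid.** The shared-data problem concerns the cost and efficiency analyses, not condom use or pregnancy. On scale, if the survival model compares clients at the same time point and recruitment is roughly concurrent (the article names no model), a shift common to all clinics cancels within risk sets. Ranks would then lose mainly the spacing between clinics and the description of change within each clinic.
- **A reader might infer that costing data exist at only two time points.** The costing subsection says costs "will be measured both at baseline and endline", but Overview of study components places costing data analysis within facility assessments at four stages. The two statements differ and need reconciling; neither can be taken as settled.

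The reply does not remove the point. The article states the inputs, the form of the output and the uses, and these conflict if followed as written. That is different from detail left to a fuller document.

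**Conclusion.** The concern holds as a risk in the cost model and as an unsuitable stated output for measuring change. Costing tools feed an index that is then used to explain unit costs, with no exclusion of overlapping items. The induced false-positive rate lies anywhere from about the nominal 5% to about 50% in the assumed scenarios, and the article gives no means of saying where. This rests on the assumed weights, the assumed item-cost correlations and a facility-level test.

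The result on ranks is exact if ranks are what is used: mean change is 0 in every set of clinics, and a stable clinic falls when others rise. If the continuous latent score is used on a common scale, that problem disappears, but the article names a ranking score and states no common scale.

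**What to change.** 1. **Cost model.** Use a version of the index that excludes every item, from the costing tools or from client flow, that also enters the numerator or denominator of unit cost. A client-flow-only index does not ensure this, because the client-flow forms record session times and the assessment counts clients per day, and both may feed unit costs. Services received per visit is an example of an item to keep. Report the full index as a sensitivity analysis.
2. **Within-facility change and dose-response.** State that the exposure is the continuous latent score, with item parameters held fixed across rounds, built only from items measured at every round used. Keep ranks for presentation and for the comparison with expert opinion.
3. **Timing.** Reconcile the two statements on when costing data are collected, since they decide which items are available at every round.

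The cost is analysis-plan wording. No new data are needed. The one downside is a somewhat narrower index in the cost model, and the sensitivity analysis shows how much that matters.

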### Data management and analysis

Statistical analyses will be both cross-sectional and longitudinal, according to the specific study component under analysis. Descriptive analyses will explore distributions and baseline associations between key exposure (provision or use of integrated services), outcomes and potentially confounding variables. Multivariable logistic regression modeling will be used to analyse study outcomes in HFA data (CPI observation data and client exit interviews), client cohort data, client flow data, community survey data and periodic activity review data.

To measure the magnitude of changes in the quality of services provided, composite summary scores will be developed from a series of key items assessed during CPIs. The composite score will be developed from a set of activities providers are required to perform or ask during history-taking for each CPI observed. The items will be based on an accepted standard of quality adapted from the national guidelines. Analyses of facility data will be undertaken and the average mean scores and the proportion of women receiving an acceptable quality of service will be calculated from the composite scores for each set of indicators.

Survival analysis will be conducted with the client cohort data to evaluate the effect of integration on key outcomes over time (up to 24 months follow-up), using two approaches: 1) comparing the cumulative probability of outcomes among clients who received services in intervention versus comparison clinics at the time of recruitment (i.e. an intent-to-treat analysis); and 2) assessing a dose–response relationship between clients’ cumulative exposure to integrated services over the duration of the study.

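### The only adjusted multi-level cost model named is a logistic regression, but cost is a continuous amount and no binary cost outcome is defined

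*Protocol article*

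**What the plan says.** The economic part of Data management and analysis closes with a regression: "a multi-level multivariable logistic regression analysis will be used to explore any association between unit costs, the intervention and integration". It proceeds in two steps. The first is described as follows: "This will first explore the relationship between patient level characteristics and costs (derived from a combination of cohort data with cost data". The second step, adjusting for the first, relates facility characteristics to costs, and on that side of the model "The integration index will be included as a facility level characteristic". Client-level cost is built by taking service use from the cohort, of which the article says "This will be combined with the unit cost data to estimate client level (health service) costs".

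The costing subsection of Description of methods and data collection says what a unit cost is: "the unit cost study will estimate the quantity and value of resources that are used to implement activities at facility level". It also gives the purpose of the regression: "The cost data will be used to conduct an econometric analysis to estimate the impact of different cost drivers, including the extent of integration". Table 3 lists the objective 3 indicators as costs per client and per person-month.

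The paragraph before the regression sets out the other cost analyses: descriptive, univariate and Data Envelopment Analysis. They cover changes between baseline and endline and comparisons between sites.

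**The concern.** Logistic regression models the probability of a binary event. Unit cost and client-level cost are amounts, and the article nowhere turns either into an event. The named model therefore does not match the named outcome.

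An analyst who followed the text literally could not fit the model. An analyst who made it work would have to choose a cost threshold, possibly after seeing the data, and would report an odds ratio that does not convert into a cost difference or ratio. What is at stake is the adjusted estimate of how integration relates to cost, allowing for who the clients are and what the facilities are like. No other multi-level cost model is named.

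**Working it through.** The article gives no sample size, power or effect size for the cost analysis, so there is no figure to reproduce. The check is of the model against the outcome, with illustrations whose inputs are assumptions.

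**1. Is cost the dependent variable?** Yes. Client characteristics are related to costs first, then facility characteristics are related to costs, and the integration index sits among the facility characteristics. Treating integration as the binary outcome and cost as the predictor does not fit that order, because the index is on the explanatory side.

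**2. Is any cost outcome binary?** No. The costing subsection describes quantities and values of resources, Table 3 lists costs per client or per person-month, and the regression paragraph combines service use with unit costs. All are amounts. No threshold appears.

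**3. Can the model be fitted as written?** A standard logistic fit to simulated positive costs stops with an error, because the outcome must lie between 0 and 1.

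**4. What would dichotomising give?** Assume log cost rises by 0.2 per SD of the index.
- Cost ratio = exp(0.2) = 1.22 per SD.
- With an assumed residual SD of log cost of 0.5 and one value for each of 32 facilities (12 + 12 + 8, Table 2), the median simulated odds ratio was 1.92 for a split at the median and 1.99 for a split at the 75th percentile.
- With a slope of 0.3, the cost ratio is exp(0.3) = 1.35 and the odds ratios are 2.84 and 2.88.
- The odds ratio also depends on residual spread. By the usual approximation, log odds ratio ≈ 1.7 × slope / SD. For slope 0.2 and SD 0.5 this is 0.68, an odds ratio of about 1.97. For SD 1.0 it is 0.34, about 1.40. The cost ratio is 1.22 in both cases, so the odds ratio does not identify it.

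**5. How much precision would a split cost?** This depends on the level at which cost enters the model.
- *One unit cost per facility.* For a normal outcome and a small effect, a median split keeps 2/π = 0.637 of the information and so loses about 36%. Simulated power (32 facilities, SD 0.5, two-sided 5%) was:

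| Slope | Linear on log cost | Median split | 75th percentile split |
|---|---|---|---|
| 0.2 | 54% | 33% | 26% |
| 0.3 | 88% | 63% | 51% |

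- *Client costs nested in facilities.* This is the structure the regression paragraph describes. With 32 facilities, 60 to 120 clients each, intraclass correlation 0.05 to 0.20, normal log cost and a median split, power for a facility-level covariate (continuous against split) was 69% against 63%, 71% against 68%, 70% against 68%, and 75% against 74%. The loss is 1 to 6 percentage points, because variation between facilities dominates.

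The main damage is therefore to interpretation. Loss of precision is substantial only if a single value per facility is analysed.

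**The case against.** The strongest defence is that this is a one-word slip in an added, exploratory analysis. The paragraph is introduced as an addition to the other cost work and is worded as exploration. The costing subsection speaks of an econometric analysis of cost drivers, which points to a continuous outcome. The article also names logistic regression for most other components, so the term may simply have been carried over. All of this is plausible, and it lowers the weight of the point. It does not remove it: the text names a specific model that does not fit its outcome, which is a misstatement and not a detail left to an analysis plan.

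Four stronger readings are tempting, and the article does not support them.

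- *Objective 3 cannot be answered.* The descriptive, univariate and Data Envelopment analyses still address unit costs and efficiency, and none needs a logistic model.
- *Most of the information is lost, or the equivalent of 11 or 12 of 32 facilities.* A median split keeps about 64%, and the conversion to facilities (32 × 0.363 = 11.6) assumes one value per facility, whereas the model nests clients.
- *The general list of logistic analyses is also wrong because it ends with* "client flow data, community survey data and periodic activity review data". The periodic activity review is described as recording facility, staffing, service and client-flow information. It is not described as cost data, and some of its items may well be binary.
- *The integration index makes the cost regression circular.* The article does say "A generalized latent variable will be modeled using data from the client flow analysis and costing tools", so exposure and outcome may share source data. It does not say which costing items enter the index. False-positive rates of 19% to 40% follow only if 20% to 30% shared error variance with opposite signs is assumed; at 5% to 10% the rate is about 6% to 9%. Nor would an index built from client flow alone cure the problem, since client flow itself records client numbers and session times.

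**Conclusion.** The point holds for the multi-level cost regression and no further. As written, the model cannot be fitted to unit cost or client-level cost. If it were rescued by an unstated cut-off, it would yield an odds ratio and not the cost difference or ratio that the costing subsection calls for. This affects the only adjusted multi-level cost analysis the article names.

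That conclusion rests on the text alone. The numerical illustrations rest on assumed slopes, residual SD, cluster sizes and intraclass correlations. Right skew in cost is a general expectation that the article does not state. Whether overlap between the index and the costing data causes bias, and how much, cannot be determined from the document.

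The point should be corrected before the cost data are analysed. Given the other planned cost analyses and the likelihood of a drafting slip, it does not undermine the economic component as a whole.

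**What to change.** In the regression paragraph of Data management and analysis, replace the logistic model with a multi-level model for a positive, skewed outcome. Either a linear mixed model on log cost or a gamma mixed model with log link would serve, with facility random intercepts and small-sample degrees of freedom for facility-level effects (12, 12 and 8 facilities per study setting in Table 2). Report adjusted cost ratios or differences with intervals. If the log-cost model is chosen, say whether the ratios are of geometric means or are transformed back to arithmetic means. If a binary cost outcome was really intended, define and justify its cut-off in advance.

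As an optional sensitivity analysis, refit the cost model with an integration index that leaves out every item, from either source, that also enters the unit-cost calculation.

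The main change costs one sentence and needs no new data. The sensitivity analysis costs one refit of the index, probably with some loss of precision in it.
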